## Abstract

**Background:**

Traditional non-steroidal anti-inflammatory drugs (NSAIDs) are a widely used class of therapy in the treatment of chronic pain and inflammation. The drugs are effective and can be relatively inexpensive thanks to available generic versions. Unfortunately the traditional NSAIDs are associated with gastrointestinal complications in a small proportion of patients, requiring costly co-therapy with gastro-protective agents. Recently, a new class of non-steroidal anti-inflammatory agents known as coxibs has become available, fashioned to be safer than the traditional NSAIDs but priced considerably higher than the traditional generics. To help physicians choose appropriately and cost-effectively from the expanded number of anti-inflammatory therapies, scientific bodies have issued clinical practice guidelines and third party payers have published restricted reimbursement policies. The objective of this study is to determine whether an educational intervention can prompt physicians to adjust their prescribing in accordance with these expert recommendations.

**Methods:**

This is an ongoing, randomized controlled trial. All primary care physicians in Manitoba, Canada have been randomly assigned to a control group or an intervention study group. The educational intervention being evaluated consists of an audit and feedback mechanism combined with optional participation in a Continuing Medical Education interactive workshop. The primary outcome of the study is the change, from pre-to post-intervention, in physicians' appropriate prescribing of non-steroidal anti-inflammatory therapies for patients requiring chronic treatment. Three classes of non-steroidal anti-inflammatory therapies have been identified: coxib therapy, traditional NSAID monotherapy, and traditional NSAID therapy combined with gastro-protective agents. Appropriate prescribing is defined based on international clinical practice guidelines and the provincial drug reimbursement policy in Manitoba.

## Background

Traditional non-steroidal anti-inflammatory drugs (NSAIDs) are a widely prescribed class of therapy used to relieve pain and inflammation. The drugs have been shown to be effective for a variety of common disorders (hence their widespread use), most notably chronic osteoarthritis and rheumatoid arthritis. They are relatively inexpensive due to the available generic versions, but unfortunately have clinically important drawbacks related to their gastrointestinal (GI) toxicity [1]. Each year, about 1% to 1.5% of patients taking traditional NSAIDs experience serious GI side effects such as perforations, ulcers, and bleeding [2-5]. When multiplied by the total number of NSAID users this translates into significant patient morbidity and mortality [1,6] and is associated with considerable health care costs related to hospitalizations or to the prescribing of expensive gastro-protective agents (GPAs) [7-12]. The cause of this GI toxicity is the "non-selective nature" of traditional NSAIDs that block both cyclo-oxygenase-2 (Cox-2), an enzyme involved in the production of inflammation and pain, and Cox-1, a related molecule that functions in GI tract mucosal protection and platelet function [13].

In the last five years, a new class of non-steroidal anti-inflammatory agents has become available to physicians, fashioned specifically to be safer than the traditional NSAIDs but priced at least two to three times higher than the generic versions of traditional NSAIDs [14]. The new drugs preferentially inhibit Cox-2 enzymes as compared to COX-1 molecules, and therefore have been christened "Cox-2 selective inhibitors" or "coxibs" for short. Large clinical trials comparing the use of coxibs to traditional NSAIDs have lent support to the concept that the new agents offer an improved GI safety profile while maintaining comparable analgesic efficacy in patients with chronic arthritis [3,4,15]. The trials, however, have also hinted that the improved GI safety may be compromised by concomitant use of low-dose aspirin [4] and may come at the expense of some cardiovascular safety, although these data remain controversial [16,17]. Regardless, the introduction of these new anti-inflammatory agents has prompted the question: when is it appropriate and cost-effective to prescribe coxibs versus traditional NSAID monotherapy or traditional NSAIDs in combination with GPAs?

To assist physicians in selecting from the different classes of anti-inflammatory agents, various scientific bodies have published clinical guidelines and third party payers have issued restricted reimbursement criteria [18-24]. These guidelines and reimbursement criteria in general propose that, for the treatment of chronic osteoarthritis and rheumatoid arthritis, coxibs should be used in lieu of traditional NSAID monotherapy when patients have an elevated risk for serious GI events. Traditional NSAID therapy in combination with certain GPAs (misoprostol or proton pump inhibitors) is also recommended as an alternative for most high-risk patients. High-risk patients are identified as individuals who have one or more of the following clinical characteristics: a history of peptic ulcer disease; advanced age (over 65 years); concomitant use of corticosteroids or anticoagulants; multiple comorbid conditions; or use of high doses or multiple NSAIDs [1,5,6,25,26]. These high-risk patients are considered to benefit from the improved GI safety of coxibs or from the GI protection afforded by GPAs. Furthermore, coxibs and GPA co-therapy have been shown to be cost-effective in such high-risk patients, as the increased cost of the drugs is partially offset by significant reductions in morbidity and mortality and related expenses [14,27-29].

With these guidelines and policies on prescribing in place, it is now important for physicians to adjust their prescribing practices accordingly. This is true both for rheumatology specialists and for physicians in the primary care setting where osteoarthritis patients are frequently managed. Unfortunately, experience and educational research show that simply making guidelines available does not elicit behavioural change from physicians [30-33]. In the case of anti-inflammatory drug prescribing, there is already evidence showing that despite the availability of guidelines and reimbursement policies, physicians' choices of drugs remain suboptimal both in terms of the inappropriate use of traditional NSAIDs and the non-cost-effective use of coxibs [34-38].

The current use of anti-inflammatory drugs suggests a need for strategies that will prompt physicians to change their prescribing practice in accordance with the expert recommendations. Preferably, strategies should be investigated that have proved successful at altering physician behaviour in other settings.

In this paper, we describe a randomized controlled study, which we are presently conducting, to evaluate the impact of an educational intervention on primary care physicians' prescribing of non-steroidal anti-inflammatory therapies. The study, being conducted in the province of Manitoba, Canada, tests the hypothesis that this intervention will significantly improve physician appropriate prescribing of anti-inflammatory drugs in compliance with international clinical practice guidelines and Manitoba's restricted drug reimbursement policy [18-22]. The intervention being tested is modelled on proven approaches to changing physician behaviour; it consists of an audit and feedback mechanism with optional participation in a Continuing Medical Education (CME) interactive workshop. This manuscript summarizes Phases II to V of a larger initiative entitled the Manitoba Appropriate Anti-Inflammatory Utilization Initiative (MAAUI). The study began in November 2000 and is currently in the data analysis stage. In this paper, we relate in detail the protocol of this randomized controlled study.

## Methods

### Study population

MAAUI is a province-wide population-based study. All primary care physicians (non-specialists) registered with the College of Physicians and Surgeons of Manitoba and practicing in Manitoba since July 1995 were eligible to enter MAAUI. The study excluded residents, new physician graduates, physicians registered as specialists, and physicians who started practicing in the province of Manitoba after July 1995. The eligible study population thus totalled approximately 884 physicians.

All eligible physicians were automatically entered into the MAAUI protocol. Physicians who were randomized to intervention group of the research were given the option to withdraw from the study. Six family physicians who agreed to act as facilitators for the MAAUI CME workshop were not included in the study population.

### Study design

The MAAUI study design is depicted in Figure 1. Primary care physicians were allocated to the control and intervention arms of the study using a stratified randomization process. Specifically, study participants were divided into groups according to the geographical area of their practice within Manitoba. These groups were stratified by physicians' "urban" (within Winnipeg – the provincial capital, population size 676,700) or "rural" (outside of Winnipeg, population size 468,300) practice location. Randomization within each stratum was then carried out at the level of the group. The MAAUI research team originally identified 12 urban and 11 rural areas in Manitoba based on existing community boundaries within Winnipeg and the presence of distinct regional health districts outside of Winnipeg. Because one urban and rural area each contained very few primary care physicians (less than five), these areas were joined to neighbouring regions resulting in 11 urban and 10 rural groups. Urban and rural groups were randomized in such a way as to achieve a 1:2 ratio of control to intervention groups. Four of the urban groups and three of the rural groups were randomized to the control arm, and the remaining seven urban and seven rural groups were randomized to the intervention arm.

This study design was chosen for several reasons. First, it offered the scientific rigour that is associated with randomization and the use of a control group. It also ensured that both rural and urban Manitoban physician groups had an equal opportunity to take part in and learn from the study intervention. The study design was also particularly amenable to testing an intervention that required physicians to congregate in common locations (i.e. for the CME workshop). The 1:2 ratio of study groups helped to ensure that there were a sufficient number of study participants who would consider attending the CME workshops.

### The educational intervention

Physicians allocated to the intervention arm of MAAUI were mailed a package that included an introduction to the study, audit and feedback material, and an invitation to participate in a CME workshop. Physicians in the control arm received no package.

#### Audit and feedback material

The audit and feedback material consisted of a "Personalised Prescribing Profile" (see Figure 2). This profile illustrated for each physician his/her recent prescribing pattern of non-steroidal anti-inflammatory therapies and the appropriateness of this prescribing pattern in light of expert recommendations. Specifically, the profile contained a bar chart showing the number of patients to whom the physician had prescribed long-term treatment with coxibs, traditional NSAID monotherapy, or traditional NSAIDs in combination with GPAs between August 1999 and September 2000. The proportion of these patients with whom the prescription was appropriate was also included. Long-term treatment was defined as patients who received therapy for a minimum of 100 days during this period. The chart, in addition to showing the physician's own prescribing profile, also showed the average profile of primary care physicians in the same geographical area and the profile of Manitoban primary care physicians overall. The reverse side of the chart listed the criteria used to define appropriate prescribing. These criteria were based on international clinical practice guidelines and Manitoba's restricted drug reimbursement policy for coxibs, and were verified by a rheumatologist on the MAAUI research team [18-22]. The criteria identified coxibs or traditional NSAID/GPA combination therapy as the appropriate choice for patients at risk for serious GI complications. The criteria also identified coxibs as the only appropriate therapy for patients with bleeding disorders or patients taking concomitant anticoagulants (this latter recommendation was based in part on Manitoba's reimbursement policy for coxibs and in part on the Canadian Consensus guidelines, and reflected concerns over the anti-platelet effect of traditional NSAIDs [18,22]). The format of the Personalised Prescribing Profiles was developed by the MAAUI research team and was validated prior to the study intervention using two focus groups of family physicians.

The Personalized Prescribing Profiles were generated by Manitoba Health and the Manitoba Centre for Health Policy (MCHP) at the University of Manitoba, using administrative data from the Population Health Research Data Repository. This repository contains anonymized encounter-based records of individuals' interactions with the provincial health care system and is derived from information received by the Department of Health, Province of Manitoba, as part of the routine provision of health care in the province. The repository includes Physician Registry files, Medical Claims and Hospital discharge files, as well as Drug Programs Information Network (DPIN) files. The DPIN contains records of all drugs dispensed by Manitoba pharmacies, regardless of who is responsible for payment.

Because of the sensitive nature of the Personalised Prescribing Profiles, the individualized profiles were not seen by the MAAUI research team. Instead the packages containing the profiles were assembled and mailed out by Manitoba Health with the assistance of an independent researcher, hired by the MAAUI research team, who signed a confidentiality agreement with Manitoba Health.

#### CME workshop

The CME workshop for MAAUI was entitled "The Utilization and Prescribing of Anti-inflammatory Drugs in Osteoarthritis". The workshop focused specifically on the prescribing for osteoarthritis, as it was felt that people with this disease account for a large proportion of the chronic non-steroidal anti-inflammatory use by primary care practices [39].

Eleven CME workshops were held throughout Manitoba (four within Winnipeg and seven outside of Winnipeg) and physicians in the intervention group were invited to voluntarily attend one of the 11. The workshops were free of charge and were approved for 3.0 hours of MAINPRO-M1 credits (continuing education credits awarded by the College of Family Physicians of Canada for group learning activities). Each workshop was facilitated by a trained family physician.

The workshops included three components: an introductory video, a decision tree, and a case study portion. The introductory video provided the history and rationale of MAAUI, explained aspects of the Personalised Prescribing Profile, and introduced the decision tree. The decision tree depicted a stepwise approach to the diagnosis and treatment of osteoarthritis. This aid was designed by a rheumatologist on the MAAUI research team specifically for use in the study and was based on international clinical practice guidelines and Manitoba's drug reimbursement policy [18-22]. A take-home copy of the decision tree was provided to each workshop participant (see Additional file 1). Finally, the case study portion of the workshop consisted of studies exploring both the diagnosis and appropriate treatment of osteoarthritis. These case studies were supplied from an existing CME curriculum entitled "Clinical Scenarios in Osteoarthritis" [40].

The overall MAAUI educational intervention, including both the audit and feedback material and the optional CME interactive workshop, was chosen by the MAAUI research team based on the success of similar interventions in the past. Audit and feedback mechanisms have shown moderate success in changing physician behaviour in past studies [41]. Equally, the addition of a continuing education workshop to an existing intervention has been shown to increase the impact on physician behaviour [42]. Workshops with interactive elements, such as case studies, have also been found to be more successful at influencing physician behaviour than purely didactic lectures [43]. Affordability, practicality, and reproducibility were also considered when designing the intervention.

### Outcomes

#### Principal outcomes

The primary goal of MAAUI is to evaluate the impact of the educational intervention on physician appropriate prescribing of non-steroidal anti-inflammatory therapies for patients requiring long-term treatment. To this end, four principal outcome measures have been developed:

• the change in appropriate prescribing of all non-steroidal anti-inflammatory therapy (including coxibs, traditional NSAIDs, and traditional NSAID/GPA combination therapy) from pre-to post-intervention;

• the change in appropriate prescribing of coxibs from pre-to post-intervention;

• the change in appropriate prescribing of traditional NSAID/GPA combination therapy from pre-to post-intervention; and

• the change in appropriate prescribing of traditional NSAID monotherapy from pre-to post-intervention.

These primary outcomes will be evaluated at the level of the individual physician and will be calculated using administrative data similar to that used to create the Personalised Prescribing Profiles. The change in appropriate prescribing (AP) for a given physician will be calculated by the physician's rate of appropriate prescribing during a 6-month period post-intervention (October 1^st ^2001 to March 31^st ^2002) minus this rate during a 10-month period immediately pre-intervention (October 1^st^, 2000 to July 31^st^, 2001). The rate of appropriate prescribing will be defined as the number of patients prescribed long-term treatment in whom the treatment was appropriate, divided by the total number of patients prescribed long-term treatment, multiplied by 100%. Otherwise expressed:

Physician's ΔAP = Post-intervention AP - Pre-intervention AP

Appropriateness of prescribing will be calculated by a researcher who is blinded to participants' study-arm allocation, and will be based on the same criteria as listed in the Personalised Prescribing Profiles (see Figure 2a). In the event that a physician has fewer than five patients on long-term treatment in either the pre- or post-intervention period, that physician's data will be withheld from analysis to ensure confidentiality of the patients.

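### Post-intervention appropriateness is scored with criteria mailed to one arm only, and the article does not exclude that a change in diagnosis recording shifts the diagnosis-based part of that score

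*Protocol article*

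**What the plan says.** All of the following is in the protocol article.

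- **Who saw the criteria.** Each intervention physician was mailed a personal profile. Audit and feedback material says: "The reverse side of the chart listed the criteria used to define appropriate prescribing". The educational intervention says: "Physicians in the control arm received no package".
- **How the outcome is scored.** Under Principal outcomes, appropriateness "will be based on the same criteria as listed in the Personalised Prescribing Profiles". The outcomes "will be calculated using administrative data similar to that used to create the Personalised Prescribing Profiles". The researcher who does the calculation is blinded to arm.
- **What the data are.** Audit and feedback material says: "The repository includes Physician Registry files, Medical Claims and Hospital discharge files, as well as Drug Programs Information Network (DPIN) files".
- **What the criteria contain.** The same section names patients at risk of serious GI complications, for whom a coxib or NSAID/GPA counts as appropriate. It also names patients with bleeding disorders or on anticoagulants, for whom only a coxib counts. The general list of risk factors in Background reads "a history of peptic ulcer disease; advanced age (over 65 years); concomitant use of corticosteroids or anticoagulants; multiple comorbid conditions; or use of high doses", and continues with use of several NSAIDs.
- **When.** The pre-intervention window ends on 31 July 2001. The post-intervention window runs from 1 October 2001 to 31 March 2002.

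**The concern.** Whether a prescription is appropriate depends on the drug and on the patient's recorded risk. The trial wants to measure a change in the choice of drug. If a diagnosis-based risk factor can be picked up from records made after mailing, the recorded risk becomes something the intervention can alter, and in one arm only. A patient already on a coxib whose ulcer history is newly recorded moves from inappropriate to appropriate with the same drug.

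Randomisation does not remove this, because the difference arises after allocation. Blinding the researcher does not remove it either, because the difference is already in the data that the researcher receives. At stake is whether a difference between arms in any of the four principal outcomes can be read as a difference in prescribing.

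**Working it through.** The article gives no figure for this effect, so there is none to reproduce. The sample size of 116 per group does not enter.

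**Step 1: which criteria recording can affect**

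| Criterion | Likely source | Open to a change in recording? |
|---|---|---|
| Age over 65 | age | no |
| Corticosteroids, anticoagulants, high-dose or multiple NSAIDs | dispensing files | no |
| Bleeding disorder | diagnosis | yes |
| Peptic ulcer history, comorbid conditions (general list in Background) | mainly diagnosis | probably |

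The dispensing rows are secure because "The DPIN contains records of all drugs dispensed by Manitoba pharmacies, regardless of who is responsible for payment".

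**Step 2: direction, with prescribing held fixed**

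Let q be the true at-risk share of a drug class, v the part of that risk visible from age or dispensing, and s the captured share of the remainder. Then:

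- detected risk = q × (v + (1 − v) × s)
- coxib and NSAID/GPA rate = detected risk
- monotherapy rate = 1 − detected risk

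If capture rises from s0 to s1, the coxib and NSAID/GPA rates rise by q(1 − v)(s1 − s0). The monotherapy rate falls by the same expression with its own q. A newly recorded bleeding disorder is an exception: it makes NSAID/GPA inappropriate, so the NSAID/GPA figures below are upper values.

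**Step 3: illustrative size**

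The values of q, v, s and the drug mix are all assumptions; none is in the documents. Take s0 = 0.50 and s1 = 0.60 or 0.75. Shifts are in percentage points.

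| v | coxib and NSAID/GPA, q = 0.7 | monotherapy, q = 0.4 | monotherapy, q = 0.7 |
|---|---|---|---|
| 0.3 | +4.9 / +12.25 | -2.8 / -7.0 | -4.9 / -12.25 |
| 0.6 | +2.8 / +7.0 | -1.6 / -4.0 | -2.8 / -7.0 |
| 0.8 | +1.4 / +3.5 | -0.8 / -2.0 | -1.4 / -3.5 |

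Largest coxib value: 0.7 × 0.7 × 0.25 = 0.1225. Smallest: 0.7 × 0.2 × 0.10 = 0.014.

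**Step 4: the all-therapy rate**

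The net shift is (share on coxib or NSAID/GPA × their q − share on monotherapy × its q) × (1 − v)(s1 − s0). At v = 0.3 and s1 = 0.75, where the last factor is 0.7 × 0.25 = 0.175:

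- 75% on coxib or NSAID/GPA, monotherapy q = 0.4: (0.75 × 0.7 − 0.25 × 0.4) × 0.175 = 0.425 × 0.175 = +7.4 points.
- Half on monotherapy, monotherapy q = 0.5: (0.5 × 0.7 − 0.5 × 0.5) × 0.175 = +1.75 points.
- Half on monotherapy, q = 0.7 throughout: (0.35 − 0.35) × 0.175 = 0.

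The net shift is negative when at-risk monotherapy patients outnumber at-risk patients on the other two classes.

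**Step 5: what a spurious 10 points would need**

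Sample size and statistics targets a 10% improvement, read here as percentage points. The rise in capture needed on the coxib rate with q = 0.7 is 0.10 / (0.7 × (1 − v)):

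- v = 0.3: 0.10 / 0.49 = 20 points
- v = 0.6: 0.10 / 0.28 = 36 points
- v = 0.8: 0.10 / 0.14 = 71 points, which is impossible from a start of 50%

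**The case against.** **The mechanism is inferred.** The article does not say which file establishes each criterion, what look-back applies, or that physicians themselves enter the diagnoses in the claims. Hospital discharge files are a further source, and ulcer history is naturally a look-back item. The list in Background describes guidelines in general, not necessarily the study's scoring sheet, and Figure 2a is not shown. An article normally leaves code lists to the full protocol. This stands, so the absence of such detail is not the point. If the full protocol already fixes risk status from records before mailing, a sentence saying so settles the matter.

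**Control physicians could know the criteria.** "These criteria were based on international clinical practice guidelines and Manitoba's restricted drug reimbursement policy for coxibs". This stands in part, but the study gave them neither the scoring list nor a personal score.

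**The effect may be small.** Age and dispensing criteria are untouched, and nothing in the article shows that coding would change. This limits the size but does not exclude the effect.

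**A stronger reading is tempting:** that better recording in the intervention arm would simply count as better prescribing. The documents do not support it. Monotherapy is one of the four principal outcomes and would move the other way, a bleeding disorder lowers the NSAID/GPA rate, and the all-therapy rate can cancel. Nor does cancellation rescue the trial, because each class is a principal outcome in its own right.

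**Fixing risk status before mailing has its own bias.** If the intervention leads a physician to identify a genuine risk after July 2001 and to prescribe according to the criteria, the frozen definition scores that choice as inappropriate. This stands, and it is why that definition should not replace the primary one.

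**Conclusion.** The concern holds in limited form. One arm was sent the scoring criteria, the same criteria score the post-intervention outcome from data of a kind that includes medical claims, and at least one criterion is a diagnosis. The article therefore does not exclude that recording, rather than prescribing, moves part of the outcome. Fuller recording would tend to inflate the coxib and NSAID/GPA results and deflate the monotherapy result, with a net all-therapy shift that may be near zero.

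The size cannot be estimated from the documents. The illustrative figures show only that the effect could range from negligible to about the size of the target improvement, and they rest wholly on assumed at-risk shares, capture and drug mix. A reader might also infer that the primary definition is wrong and must be replaced. The documents do not support that: both definitions are imperfect, and the operational details are not shown.

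**What to change.** Keep the stated primary definition and add:

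1. **A sensitivity analysis of all four principal outcomes.** For both periods, take diagnosis-based risk status only from records dated up to 31 July 2001. Continue to take age and dispensed drugs from each window.
2. **A table by arm** of the frequency of qualifying diagnoses first recorded after mailing.
3. **A reading rule fixed in advance.** If the two definitions disagree, the difference is not attributed to prescribing alone.

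The cost is a date restriction on the diagnosis records, a rerun of the analysis and one table, from the same data sources. The article puts the study at the data analysis stage, so this should be labelled as an addition and not as a new primary outcome. The downside is that the frozen definition misses risks genuinely identified after July 2001, possibly more often in the intervention arm. It may then understate a true effect and should be reported as a bound.
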